#### **\*\*3.2.2 Exclusion Criteria\*\***

- (1) Limb motor dysfunction caused by other diseases;
- (2) Presence of psychiatric system diseases or cognitive dysfunction preventing cooperation with rehabilitation training and taVNS therapy;

- (3) Unstable vital signs;
- (4) Implanted cardiac pacemaker, uncontrolled epilepsy, history of vasovagal syncope, or other contraindications for taVNS.

#### **\*\*3.2.3 Withdrawal Criteria\*\***

- (1) Patient's condition changes requiring transfer to another department or inability to complete standardized treatment;
- (2) Unstable vital signs during treatment or recurrence of stroke;
- (3) Intolerance to taVNS treatment, etc.

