#### **\*\*3.3 Study Groups and Interventions\*\***

To verify the clinical efficacy and safety of bilateral taVNS for stroke motor dysfunction, and its difference compared to unilateral left-sided taVNS, this clinical trial is divided into three groups:

- (1) **\*\*Conventional Treatment Group:\*\*** Based on drug therapy, provide conventional rehabilitation treatment for stroke hemiplegic motor dysfunction, including comprehensive rehabilitation such as exercise therapy, occupational therapy, physical agent therapy, conventional acupuncture, etc.
- (2) **\*\*Left-sided taVNS Group:\*\*** Based on the conventional treatment group, provide classic non-invasive left-sided auricular vagus nerve electrical stimulation. taVNS parameters: left ear, frequency 25Hz, pulse width 300us, current 6 mA.
- (3) **\*\*Bilateral taVNS Group:\*\*** Based on the conventional treatment group, provide non-invasive bilateral auricular vagus nerve electrical stimulation. taVNS parameters: both ears, frequency 25Hz, pulse width 300us, current 6 mA.

**\*\*taVNS Treatment Regimen:\*\*** 30min/session, 2 sessions/day, 6 days/week, for 4 weeks.

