#### **\*\*3.6 Study Procedures\*\***

Study steps mainly include clinical trial randomization and grouping, follow-up and data collection at baseline (T0), at 2 weeks of treatment (T1), at the end of 4 weeks (T2), and at 8 weeks after treatment completion (T3), as detailed below:

- (1) **\*\*Randomization and Grouping:\*\*** Enroll eligible stroke patients with motor dysfunction and assign them to the Conventional Treatment Group, Left-sided taVNS Group, or Bilateral

taVNS Group using a random number table.

(2) **\*\*Collection of Basic Patient History Information:\*\*** Collect basic information for enrolled subjects, including age, gender, time since onset, stroke type, education level, marital status, etc.

(3) **\*\*Data Collection at T0, T1, T2 time points:\*\*** Fugl-Meyer Assessment for Upper Extremity (FMA-UE) and Lower Extremity (FMA-LE), Wolf Motor Function Test (WMFT), Balance evaluation and training system, Berg Balance Scale (BBS), Holden Functional Ambulation Classification (FAC), Modified Barthel Index (MBI), functional Near-Infrared Spectroscopy (fNIRS).

(4) **\*\*Data Collection at T3 follow-up time point:\*\*** Follow up via phone or outpatient visit to collect Berg Balance Scale (BBS) and Modified Barthel Index (MBI) scores at 8 weeks after treatment completion.

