#### **\*\*4.2 Adverse Event Handling, Follow-up, and Serious Adverse Event Reporting\*\***

> The investigator shall explain in detail to the subject, requiring the subject to truthfully report any changes in condition after receiving the intervention treatment. Physicians should avoid leading questions. While observing efficacy, close attention should be paid to adverse events, analyzing causes and making judgments. For any AE occurring during the study, details such as time of onset, symptoms, duration, measures taken, and outcome should be recorded in the medical record/Case Report Form, and its relationship to the investigational intervention should be assessed; for those with abnormal laboratory findings, follow up until results return to normal or to pre-treatment levels. In case of an SAE, a Serious Adverse Event Form should be completed and reported to the Hospital Medical Ethics Committee and the IIT Project Management Office within 24 hours.

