## **\*\*6. Statistical Analysis Plan\*\***

### **\*\*6.1 Sample Size Estimation\*\***

Sample size was determined using  $N = 2 \cdot [(Z_{\alpha/2} + Z_{\beta})\sigma/d]^2$  and statistical power analysis software G\*Power 3.1. Referring to the effect size observed in studies like Dawson et al. (Cohen's  $d=0.632$ ), with  $\alpha=0.05$  and statistical power  $(1-\beta)$  equal to 80%, the estimated sample size per group should be 34. Considering a 10% clinical dropout rate, the sample size per group was adjusted to 38, totaling 114 participants across three groups.

\*Reference: Dawson J, et al. Vagus nerve stimulation paired with rehabilitation for upper limb motor function after ischaemic stroke (VNS-REHAB): a randomised, blinded, pivotal, device trial. Lancet. (2021) 397:1545–53.\*

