### **\*\*6.3 Analysis Populations\*\***

Subjects who do not comply with the study protocol will be excluded from the analysis.

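### Section 6.3 excludes non-compliers and section 3.2.3 does not separate stopping treatment from leaving the study, so randomised patients can be lost from the primary FMA comparison for post-randomisation reasons

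*Protocol*

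**What the plan says.** Section 3.2.3 of the protocol gives three withdrawal criteria: "Patient's condition changes requiring transfer to another department or inability to complete standardized treatment", "Unstable vital signs during treatment or recurrence of stroke" and "Intolerance to taVNS treatment, etc". All three are reasons why treatment may have to stop. The section does not say what happens to the patient's assessments afterwards.

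Section 6.3, on analysis populations, is a single sentence: "Subjects who do not comply with the study protocol will be excluded from the analysis". It names no all-randomised set.

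Section 3.6 places the visits after baseline "at 2 weeks of treatment (T1), at the end of 4 weeks (T2), and at 8 weeks after treatment completion (T3". FMA-UE and FMA-LE, the primary endpoints in section 3.8.1, are collected at T0, T1 and T2. T3 collects only BBS and MBI.

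Section 3.3 gives taVNS to two of the three arms and lists no sham stimulation for the conventional arm. Section 6.1 allows for loss at one common rate: "Considering a 10% clinical dropout rate, the sample size per group was adjusted to 38".

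**The concern.** A randomised comparison is protected only while patients stay in the analysis in the arm to which they were allocated. Section 6.3 removes patients on the basis of behaviour after randomisation. Section 3.2.3 gives a list of post-randomisation events under a heading that can be taken to mean leaving the study. If a site takes it that way, a patient who stops in week 1 may have no further FMA. The primary endpoint is not measured at T3, so it cannot be picked up later.

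The visit wording adds to the difficulty. T1 is tied to weeks of treatment and T3 to treatment completion, and neither is well defined for someone who stops early. T2 is less affected, because its wording can be read as calendar time.

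At stake is whether the trial estimates the effect of assigning taVNS or a comparison among those who tolerated and completed it. The two differ if loss, or the link between loss and outcome, differs between arms. This is not simply a detail left to a statistical analysis plan. Section 6.3 positively fixes an exclusion, and no later document can restore FMA values that were never collected.

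**Working it through.** **Step 1: the plan's own figure.** Section 6.1 starts from 34 per group and allows 10% dropout: 34 / (1 − 0.10) = 37.8, rounded up to 38, and 3 × 38 = 114. The allowance reproduces. It is a single rate for all arms and says nothing about reasons for loss. How the 34 arises does not matter here.

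**Step 2: which withdrawal reasons can arise in which arm** (section 3.2.3 against the arms in section 3.3).

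| Reason | Conventional | Left taVNS | Bilateral taVNS |
|---|---|---|---|
| Transfer, or treatment not completed | yes | yes | yes |
| Unstable vital signs, recurrent stroke | yes | yes | yes |
| taVNS intolerance | no, as the arm is defined | yes | yes |

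Only the last row separates the arms, and it separates taVNS from conventional treatment. In the bilateral-versus-left contrast intolerance can arise on both sides, possibly at different rates.

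**Step 3: formula.** Let a share p of an arm be left out, and let those patients be k SD worse on average than the rest of their arm. The mean of those kept then exceeds the all-randomised mean by p × k. The bias in taVNS minus conventional is

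pT × kT − pC × kC.

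If p and k are the same in both arms, for example 10% lost from each, this is 0. Equal rates alone are not enough; the deficit must match too.

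**Step 4: numbers.** Inputs: 0.632 SD is the planning effect in section 6.1. The excess loss d in a taVNS arm is an assumption, taken as 0.05 to 0.10, because the documents give no rate. A further assumption is that the excess patients lose exactly the planned benefit, k = 0.632. Base loss is taken as equal in rate and deficit, so it cancels and the bias is d × 0.632. The standard error of a two-arm comparison at 34 per group is √(2/34) = 0.2425 SD.

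| | d = 0.05 | d = 0.10 |
|---|---|---|
| Extra patients lost, of 38 | 1.9 | 3.8 |
| Bias, d × 0.632 (SD) | 0.0316 | 0.0632 |
| Effect among those kept (SD) | 0.632 | 0.632 |
| All-randomised effect, 0.632 × (1 − d) (SD) | 0.600 | 0.569 |
| Bias / 0.632 | 5% | 10% |
| Bias / standard error | 0.13 | 0.26 |

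**Step 5: what the mixed model could recover.** Section 6.2 plans a linear mixed model. Suppose patients who stop after T1 stay in it with their T0 and T1 values. With a common between-visit correlation ρ, the share of the bias that remains is 1 − s × ρ / (1 + ρ), where s is the part of the T2 deficit already visible at T1. Assume ρ = 0.6, so ρ / (1 + ρ) = 0.375:

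- s = 0.5: share 0.8125, bias 0.026 (d = 0.05) to 0.051 SD (d = 0.10).
- s = 1: share 0.625, bias 0.020 to 0.040 SD.

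Excluding the patient under section 6.3 gives up this recovery.

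**The case against.** The link between the sections is inferred. Section 3.2.3 does not say that assessment ends. A patient withdrawn under a criterion that the protocol itself sets can be regarded as handled in line with the protocol, so section 6.3 need not apply. T2, the last FMA visit, can be read as a calendar visit open to someone who has stopped. All of this stands, and the point is therefore what the sections allow, not what they command. It does not remove the point: section 6.3 still excludes non-compliers, and nothing tells a site to keep assessing a patient who stops.

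The asymmetry also depends on the arms as section 3.3 lists them. The synopsis and the background section call the trial sham-randomized, and section 3.5 claims double blinding. If the conventional arm did receive a sham, intolerance could arise there too. That conflict is unresolved in the protocol.

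A reader might infer two further things that the documents do not support:

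- Only taVNS has a numeric schedule, "30min/session, 2 sessions/day, 6 days/week, for 4 weeks", which might suggest that non-compliance will be detected only in those arms. Nothing says that compliance is judged by counting sessions, and the treatment to be completed may include the conventional rehabilitation given to everyone.
- Adverse events leading to withdrawal might be thought to go unrecorded. Section 4.2 requires otherwise: "For any AE occurring during the study, details such as time of onset, symptoms, duration, measures taken, and outcome should be recorded".

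**Conclusion.** The point holds as a weakness in wording that leaves the primary comparison unprotected. Sections 3.2.3 and 6.3 together permit post-randomisation loss or exclusion from the FMA-UE and FMA-LE analysis, and one listed reason is specific to taVNS as the arms are defined.

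The size cannot be derived from the documents and is probably small: 0.03 to 0.06 SD under the assumed 5 to 10 points of excess loss and full loss of the planned benefit. It is less if some benefit is kept or if T1 values stay in the model, and zero if loss and deficit are equal. The only tolerability evidence in the protocol, an earlier left-sided taVNS trial in another population with no related adverse reactions, points to the lower end, though it does not cover bilateral stimulation.

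A reader might go further and infer an inflated false-positive rate. Losing a benefit cannot create an effect where none exists; for that, those who stop must also have a worse prognosis. For illustration, with no true effect, removing 10% of one taVNS arm selected on a variable correlated 0.5 with outcome gives a spurious 0.10 SD and a type I error of about 7%. The documents support neither input, so this is not part of the conclusion. The T3 timing gap affects BBS and MBI only, which are secondary.

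**What to change.** Three changes of wording:

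- **Section 6.3:** *The primary analysis includes all randomised participants in their randomised group, including those who stop the study intervention; a per-protocol set is used for sensitivity analysis only.*
- **Section 3.2.3:** retitle as *Criteria for discontinuing the study intervention*, keep the clinical reasons, and add: *Participants who stop the study intervention remain in the study and complete all scheduled T1, T2 and T3 clinical assessments where medically feasible; date and reason for stopping are recorded; only withdrawal of consent, death or loss to contact ends data collection.*
- **Section 3.6:** time T1, T2 and T3 at 2, 4 and 12 weeks from randomisation in all arms, or from planned treatment start if that is set the same way in every arm. For a patient who starts at randomisation and completes treatment, 4 + 8 = 12 weeks is the present T3.

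The cost is the protocol text and one case report form page for the date and reason for stopping. No new type of assessment is needed, and the planned 38 per group stays. The downside is practical: some patients who stop must be assessed on another ward or recalled, and FMA will not be feasible in some after a new stroke. The change helps only patients whose visits are still to come, because values not collected cannot be recovered.

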#### **\*\*3.3 Study Groups and Interventions\*\***

To verify the clinical efficacy and safety of bilateral taVNS for stroke motor dysfunction, and its difference compared to unilateral left-sided taVNS, this clinical trial is divided into three groups:

- (1) **\*\*Conventional Treatment Group:\*\*** Based on drug therapy, provide conventional rehabilitation treatment for stroke hemiplegic motor dysfunction, including comprehensive rehabilitation such as exercise therapy, occupational therapy, physical agent therapy, conventional acupuncture, etc.
- (2) **\*\*Left-sided taVNS Group:\*\*** Based on the conventional treatment group, provide classic non-invasive left-sided auricular vagus nerve electrical stimulation. taVNS parameters: left ear, frequency 25Hz, pulse width 300us, current 6 mA.
- (3) **\*\*Bilateral taVNS Group:\*\*** Based on the conventional treatment group, provide non-invasive bilateral auricular vagus nerve electrical stimulation. taVNS parameters: both ears, frequency 25Hz, pulse width 300us, current 6 mA.

**\*\*taVNS Treatment Regimen:\*\*** 30min/session, 2 sessions/day, 6 days/week, for 4 weeks.

#### **\*\*3.4 Randomization\*\***

##### **\*\*3.4.1 Method for Generating Random Allocation Sequence\*\***

> Use a random number table for randomization.

##### **\*\*3.4.2 Allocation Concealment\*\***

Central randomization.

##### **\*\*3.5 Blinding and Unblinding\*\***

Double-blind design will be used.

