## \*\*Protocol Synopsis\*\*

| **\*\*Study Title\*\*** | Bilateral Auricular Vagus Nerve Stimulation for Promoting Motor Function Reconstruction after Stroke: A Prospective, Safety, Multicenter, Randomized Controlled Study

\_\_\_\_\_

\_\_\_\_\_

\_\_\_\_\_

\_\_\_\_\_

| **Study Objective** | This project aims to observe the therapeutic effect and safety of bilateral auricular vagus nerve electrical stimulation on motor dysfunction reconstruction after stroke, and to elucidate its brain function rehabilitation mechanism using fNIRS technology, thereby laying a theoretical foundation for the clinical application of bilateral auricular vagus nerve electrical stimulation in treating post-stroke motor dysfunction. |

| **Study Design** | Prospective, multicenter, sham-randomized controlled study |

| **Study Population** | **Inclusion Criteria:** (1) Age between 18 and 65 years; (2) Diagnosed with stroke (including ischemic stroke and hemorrhagic stroke) by a qualified clinician according to the "Chinese Stroke Prevention and Treatment Guidelines" from 2021 onwards; (3) Stroke recovery period, stable vital signs, no disease progression; (4) Presence of limb motor dysfunction, diagnosed with hemiplegia. **Exclusion Criteria:** (1) Limb motor dysfunction caused by other diseases; (2) Presence of psychiatric system diseases or cognitive dysfunction preventing cooperation with rehabilitation training and taVNS therapy; (3) Unstable vital signs; (4) Implanted cardiac pacemaker, uncontrolled epilepsy, history of vasovagal syncope, or other contraindications for taVNS. |

| **Interventions** | (1) **Conventional Treatment Group:** Based on drug therapy, provide conventional rehabilitation treatment for stroke hemiplegic motor dysfunction, including comprehensive rehabilitation such as exercise therapy, occupational therapy, physical agent therapy, conventional acupuncture, etc. (2) **Left-sided taVNS Group:** Based on the conventional treatment group, provide classic non-invasive left-sided auricular vagus nerve electrical stimulation. taVNS parameters: left ear, frequency 25Hz, pulse width 300us, current 6 mA. (3) **Bilateral taVNS Group:** Based on the conventional treatment group, provide non-invasive bilateral auricular vagus nerve electrical stimulation. taVNS parameters: both ears, frequency 25Hz, pulse width 300us, current 6 mA. |

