However, there are still some shortcomings in VNS for treating post-stroke motor dysfunction. \*\*VNS techniques are mainly invasive implants or left-sided unilateral taVNS, the observation subjects are mainly upper limb motor dysfunction after stroke, and there is a lack of large-sample, multicenter randomized controlled trials.\*\* Furthermore, literature suggests that activating \*\*bilateral auricular vagus nerves can increase sensory input to brainstem neural pathways, enhancing the therapeutic effect of VNS, with effects superior to unilateral taVNS\*\*^[16]^ . Based on this, this project intends to use bilateral taVNS as the intervention, target upper and lower limb motor dysfunction after stroke, and conduct a prospective, multicenter, sham-randomized controlled study to clarify the clinical efficacy and safety of bilateral taVNS for treating upper and lower limb motor dysfunction after stroke, and to elucidate the brain function rehabilitation mechanism of taVNS in treating post-stroke motor dysfunction.

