## **\*\*3. Study Overview\*\***

**\*\*3.1 Overall Study Design:\*\*** This is a prospective, safety, multicenter, randomized controlled study.

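### Protocol section 3.5 promises a double-blind design and the synopsis a sham, but the three arms contain no sham, so patients and treating therapists cannot be blind as written

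*Protocol*

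**What the plan says.** Section 3.5 (Blinding and Unblinding) reads in full "Double-blind design will be used". It names no masked role and no method.

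The synopsis, under Study Design, describes a "Prospective, multicenter, sham-randomized controlled study". The end of section 1(3) repeats this as the plan to "conduct a prospective, multicenter, sham-randomized controlled study". Section 3.1 uses neither term: "This is a prospective, safety, multicenter, randomized controlled study".

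Section 3.3 says "this clinical trial is divided into three groups":
- The control arm is to "provide conventional rehabilitation treatment for stroke hemiplegic motor dysfunction, including comprehensive rehabilitation such as exercise therapy", with further therapies listed and no device.
- The left-sided arm adds active stimulation of the left ear.
- The bilateral arm adds active stimulation, with "taVNS parameters: both ears, frequency 25Hz, pulse width 300us, current 6 mA".

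The taVNS regimen in 3.3 is 30 minutes per session, 2 sessions a day, 6 days a week, for 4 weeks. The primary endpoints (3.8.1) are FMA-UE and FMA-LE.

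**The concern.** Double-blind and sham-controlled are claims about design, and readers of the eventual report will weigh the result by them. The arms described cannot deliver either. FMA is scored by a rater from what the patient does, so it is open to patient effort and to the rater's judgement. If patients know whether they have no, one or two stimulated ears, expectation can favour taVNS over rehabilitation alone, and plausibly bilateral over left. These are the contrasts that section 3.3 sets out to test.

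The planning assumption also comes from a different setting. Section 6.1 takes d = 0.632 from a trial whose cited title calls it blinded, and section 1(3) describes that line of work as comparing implanted stimulation with a sham. Here the comparator is no device at all.

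**Working it through.** **Step 1. Compare the label with the arms.** The protocol contains no figure for blinding to reproduce, so the main check is of text against text.

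| Place | Sham? | Blinding? |
|---|---|---|
| Synopsis, Study Design | claimed | not mentioned |
| Section 1(3), plan for this trial | claimed | not mentioned |
| 3.1 Overall design | not mentioned | not mentioned |
| 3.3 Arms | none described | none described |
| 3.5 Blinding | not mentioned | double-blind claimed |
| 3.6 Procedures, 3.7 Concomitant treatment | none described | no masked assessor described |

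The only other use of sham and double-blind is in section 1(3), for earlier trials of implanted stimulation.

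**Step 2. What each party can see.** Stimulated ears by arm: control 0, left-sided 1, bilateral 2. No inactive electrode is described for the control arm or for the right ear of the left-sided arm. The patient and whoever applies the device can tell all three arms apart. This is an inference, but it follows directly from the arms as described.

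**Step 3. Device exposure (inputs from 3.3).**
- Sessions per taVNS arm: 2 × 6 × 4 = 48.
- Device time: 48 × 0.5 h = 24 h.
- Control arm: 0 sessions, 0 h.

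The two taVNS arms have equal session counts, so between them only the number of ears differs.

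**Step 4. What a given bias would do (illustration).** Inputs: n = 34 per arm before dropout and two-sided alpha 0.05, both from 6.1. The bias b, in SD units, is assumed, because the documents give none. The true effect is zero.

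For a two-sample t-test, df = 2 × 34 − 2 = 66, the critical value is 1.997 and the noncentrality is b × √(34/2).

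| b (SD) | Noncentrality | Rejects, either direction | Rejects in favour of taVNS | b / 0.632 |
|---|---|---|---|---|
| 0 | 0 | 5.0% | 2.5% | 0% |
| 0.1 | 0.412 | 6.9% | 6.0% | 16% |
| 0.2 | 0.825 | 12.8% | 12.6% | 32% |
| 0.3 | 1.237 | 23.0% | 22.9% | 47% |

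Section 6.2 plans a linear mixed model, so these rates show the order of size and do not predict that analysis.

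**The case against.** The strongest reply is that 3.5 names no roles. Masked assessors and a masked analyst are not excluded, and an analysis plan that is not shown might describe them. That is right as far as it goes. A reader might infer that nobody in the trial is blind, or that the FMA raters know the allocation. The protocol supports neither: it is silent on raters. What is shown is limited to patients and treating therapists. Even so, masking the raters alone would not make this a double-blind trial in the usual sense, and no analysis plan can supply a sham that the arms lack.

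Several further limits stand:
- A reader might take the 24 hours as extra staff contact. Section 3.3 gives stimulation time only. It does not say that staff attend throughout, or that stimulation falls outside rehabilitation time. The control arm lacks taVNS sessions but does receive its own therapies.
- A reader might conclude that the bilateral-versus-left comparison must be dropped. Lack of blinding is no ground for that. It is a stated aim in 3.3 and can be reported as an open comparison.
- The bias range is an assumption. At its low end the inflation is small, and the finding does not depend on it.
- Inactive electrodes on the unallocated ears might look like an easy rescue of the label. Nothing in the documents shows that patients could not feel the difference between current and no current, or that whoever sets the device would stay masked. Section 9 mentions bilateral devices only for the lead department.
- Sham may be a slip of translation. The double-blind sentence in 3.5 would still conflict with the arms.

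**Conclusion.** The protocol claims a property that its design does not have. Section 3.5, the synopsis and the plan at the end of section 1(3) contradict the arms in 3.3. With no sham in any arm, patients and treating therapists cannot be blind as written, and no masking of FMA raters is described. Expectation and attention effects therefore cannot be separated from a stimulation effect.

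The contradiction rests on the text alone. That patients and therapists know the allocation rests on the arms being delivered as described. The size of the resulting bias is unknown: the rates of about 7%, 13% and 23% hold only for assumed biases of 0.1, 0.2 and 0.3 SD, 34 per arm and a simple t-test. The point must be fixed, because the primary endpoints are rater-scored and the correction is cheap.

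**What to change.** 1. Replace section 3.5 with: *Treatment is open to patients and therapists. FMA and the other rater-scored outcomes are assessed by trained staff at each centre who do not treat that patient and are not told the allocation. The analyst works with coded arms.*
2. In the synopsis (Study Design) and in the description of this trial at the end of section 1(3), change sham-randomized controlled to randomized controlled. Leave the account of the earlier implanted-stimulation trials in section 1(3) as it is; those words describe other studies.
3. Report taVNS versus rehabilitation alone, and bilateral versus left taVNS, as comparisons open to patients and therapists, with no claim of sham-controlled or double-blind evidence.

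Cost: the double-blind label is lost. The change is a protocol revision and needs ethics committee approval before use (section 7.1). Each of the three centres must roster raters to patients they do not treat. Section 10 already schedules training in scale administration, but it does not provide for separate raters, so the rota has to be planned. No arm, stimulation parameter or visit changes.
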